# Efficacy and safety of Lenzumestrocel (Neuronata-R**®** inj.) in patients with amyotrophic lateral sclerosis (ALSUMMIT study): study protocol for a multicentre, randomized, double-blind, parallel-group, sham procedure-controlled, phase III trial

**DOI:** 10.1186/s13063-022-06327-4

**Published:** 2022-05-18

**Keywords:** Lenzumestrocel, Amyotrophic lateral sclerosis, Bone marrow-derived mesenchymal stem cell, Phase III

## Abstract

**Background:**

A single cycle (two repeated treatments) with intrathecal autologous bone marrow-derived mesenchymal stem cells (BM-MSCs, 26-day interval) showed safety and provided therapeutic benefit lasting 6 months in patients with ALS but did not demonstrate long-term efficacy. This phase III clinical trial (ALSUMMIT) protocol was developed to evaluate the long-term efficacy and safety of the combined protocol of single-cycle intrathecal therapy and three additional booster injections of BM-MSC (Lenzumestrocel) treatment in patients with ALS.

**Methods:**

ALSUMMIT is a multicentre, randomized, double-blind, parallel-group, sham procedure-controlled, phase III trial for ALS. The 115 subjects will be randomized (1:2:2) into three groups: (1) study Group 1 (single-cycle, two repeated injections with 26-day interval), (2) study Group 2 (single-cycle + three additional booster injections at 4, 7, and 10 months), and (3) the control group. Participants who have an intermediate rate of disease progression will be included in this trial to reduce clinical heterogeneity. The primary endpoint will be evaluated by combined assessment of function and survival (CAFS), also known as joint rank scores (JRS), at 6 months (study Group 1 vs. control) and 12 months (study Group 2 vs. control) after the first Lenzumestrocel or placebo administration. Safety assessment will be performed throughout the study period. Additionally, after the 56-week main study, a long-term follow-up observational study will be conducted to evaluate the long-term efficacy and safety up to 36 months.

**Discussion:**

Lenzumestrocel is the orphan cell therapy product for ALS conditionally approved by the South Korea Ministry of Food and Drug Safety (MFDS). This ALSUMMIT protocol was developed for the adoption of enrichment enrolment, add-on design, and consideration of ethical issues for the placebo group.

**Trial registration:**

ClinicalTrials.govNCT04745299. Registered on Feb 9, 2021.

Clinical Research Information Service (CRIS) KCT0005954. Registered on Mar 4, 2021.

**Supplementary Information:**

The online version contains supplementary material available at 10.1186/s13063-022-06327-4.

## Administrative information

Note: the numbers in curly brackets in this protocol refer to SPIRIT checklist item numbers. The order of the items has been modified to group similar items (see http://www.equator-network.org/reporting-guidelines/spirit-2013-statement-defining-standard-protocol-items-for-clinical-trials/).

## Introduction

### Background and rationale {6a}

Amyotrophic lateral sclerosis (ALS), which is known as Lou Gehrig’s disease, is a neurodegenerative disease characterized by progressive loss of selective motor neurons in the brain, brain stem, and spinal cord, which leads to progressive weakness with a fatal outcome due to paralyzed respiratory muscles within a mean of 2–4 years after diagnosis [1, 2]. Riluzole and edaravone are the only approved drugs by the Food and Drug Administration (FDA) with modest treatment effects on ALS progression [3, 4]. While the pathogenic mechanisms of sporadic ALS cases remain unknown, genetic mutations linked to the disease have provided a more accessible target for therapeutic development [5]. The development of therapies that specifically target known ALS mutations, including *chromosome 9 open reading frame 72* (*C9orf72*) and *superoxide dismutase 1* (*SOD1*), *fused in sarcoma* (*FUS*), has been rapidly evolving in recent years [6–8]. Despite the emerging precision of medicine in the genetic cause of ALS, more than 90~95% of patients present with sporadic ALS, and their clinical manifestations are more heterogeneous [9]. Lessons from previous failed trials focused on a single molecular target have led us to develop a therapeutic strategy aimed at multiple targets related to non-cell-autonomous toxicity.

Mesenchymal stem cell (MSC) therapy is a promising therapeutic strategy for addressing this issue. MSCs have been shown to exert diverse effects, such as stimulating intrinsic neurogenesis, releasing diverse neurotrophic factors, and modulating immunoinflammatory processes [10–13].

Lenzumestrocel (Korean product name; Neuronata-R® inj.) is an autologous bone marrow-derived mesenchymal stem cell and was designated as an orphan drug for concomitant therapy with riluzole in patients with ALS under the Revised Rule of Orphan Drug Designation by the Korea Ministry of Food and Drug Safety (Dec 31, 2013, MFDS Announcement No. 2013-262). In a previous phase II clinical trial, two repeated treatments with intrathecal autologous BM-MSCs (26-day interval) showed a therapeutic benefit lasting only 6 months, with good safety, in patients with ALS [14].

ALSUMMIT aims to evaluate the efficacy and long-term safety of two repeated (single-cycle) Lenzumestrocel intrathecal treatments by extending the study period. Additionally, we will assess the safety and efficacy of single-cycle + three additional booster injections. A post hoc survival analysis in our phase II trial did not show a long-term survival benefit. This may be associated with two limited injections with therapeutic effects that were not long-lasting. Considering the immunomodulatory effects of BM-MSC treatment by intrathecal delivery (less-invasive procedures), it would be essential to determine whether successive booster BM-MSC treatments after single-cycle treatment could improve long-term efficacy.

### Objectives {7}

The purpose of this study is to demonstrate the clinical superiority of Lenzumestrocel after its administration compared to a placebo. The two primary endpoints will be evaluated by comparing the therapeutic efficacy between (1) study Group 1 (single-cycle, two repeated injections of Lenzumestrocel with 26-day interval) and the control group (two administrations of the placebo) at 6 months and (2) study Group 2 (single-cycle + three additional booster injections of Lenzumestrocel) and the control group (five administrations of the placebo) at 12 months in terms of joint rank scores (JRS), also known as the combined assessment of function and survival (CAFS). The secondary endpoint will be evaluated by comparing the therapeutic efficacy between study Group 2 and the control group at 6 months in terms of JRS, change in ALSFRS-R score from baseline, and time to event at individually specified points after administration. Additionally, as the exploratory endpoint, this study will investigate pulmonary function (slow vital capacity, SVC), muscular strength (hand-held dynamometry, HHD), time-to-event, and time-to-death. Finally, serially collected biological specimens during clinical trials will be used to develop biological markers to predict the efficacy and analyse the mode of action of Lenzumestrocel.

### Trial design {8}

ALSUMMIT is a multicentre, randomized, double-blind, parallel-group, sham procedure-controlled, phase III clinical trial to evaluate the efficacy and safety of Lenzumestrocel in patients with ALS. This clinical trial consists of the main study (within a 17-week lead-in period and a 14-month treatment period) and an additional observational study (Fig. 1). Among participants, patients who wish to participate in further long-term observation studies will be followed up to 3 years after the first treatment. Randomization will be conducted by the stratified block randomization method considering the stratification factors Riluzole administration (Y or N) and ALS types (bulbar or limb) to ensure that subjects are randomly assigned to study Group 1, study Group 2, and the control group in a ratio of 1:2:2.

**Fig. 1 Fig1:**
[figure not shown]
Overview of ALSUMMIT trial design. Data from study Group 1 and the control group will be analysed by JRS score at 6 months after the single-cycle treatments. Study Group 2 and the control group will be analysed by JRS score at 12 months after the combined single-cycle intrathecal therapy and three additional booster injections of MSC (Lenzumestrocel) treatment. CSF, cerebrospinal fluid; ALSFRS-R, Amyotrophic Lateral Sclerosis Functional Rating Scale-revised; JRS, joint rank score

The ALSUMMIT protocol was developed for the adoption of enrichment enrolment and add-on design and consideration of ethical issues for the placebo group.

A total of 115 subjects who meet the criteria for eligibility and the inclusion/exclusion criteria will be randomly assigned using the Interactive Web Response System (IWRS) to study Group 1, study Group 2, or the control group. Details of the eligibility and the inclusion/exclusion criteria are described in the eligibility criteria section. All subjects will be observed for 14 months after the first administration of Lenzumestrocel or placebo.

## Methods: participants, interventions, and outcomes

### Study setting {9}

The ALSUMMIT trial will be conducted in South Korea at five academic hospitals (Hanyang University Hospital, Korea University Anam Hospital, Samsung Medical Center, Seoul National University Hospital, and Pusan National University Yangsan Hospital). All data will be collected at each site.

### Eligibility criteria {10}

Participants who meet the following criteria will be included in this clinical trial:Participants aged 25 to 75 years.Participants showing both upper motor neuron signs (hyperactive deep tendon reflexes, positive Babinski reflex, positive ankle clonus, positive Hoffman reflex and increased muscle tone) and lower motor neuron signs (muscle wasting, muscle weakness, and fasciculation) at the time of neurological examination.Participants diagnosed as familial or sporadic ALS compatible with clinically definite ALS, probable ALS, or probable ALS-lab supported, following the revised World Federation of Neurology El Escorial criteria [15].Participants who show an ALSFRS-R progression rate of 1.03±0.52/month during a 17-week lead-in period prior to treatment administration.Participants who have received a stable dose of riluzole for more than 28 days before the screening visit. However, it does not apply to participants whose riluzole administration is deemed impossible due to adverse events as determined by neurologists.Participants have a disease duration less than 2 years from the date of initial diagnosis.Participant whose ALSFRS-R score in the range of 31 to 46 at the time of screening.Participants who can visit the site by themselves or with others' support.Participants and/or their guardians who give consent to participate in this clinical trial.

Patients who meet the following criteria will be excluded from this clinical trial:Patients who fail to satisfy the ALS diagnosis criteria, as per the revised World Federation of Neurology El Escorial Criteria.Patients with primary lateral sclerosis that show only upper motor neuron signs or with progressive muscular atrophy, or low motor neuron disease that show only lower motor neuron signs.Patients expected to have side effects on the administration of cell therapy (i.e. patients suspected to have malignant tumours, high-risk patients vulnerable to psychogenic shock, and severe hypertension).Patients with ALSFRS-R scores of less than 31 at the time of screening.Patients who received tracheostomy or use ventilators (including positive pressure ventilators; patients who use noninvasive ventilation for sleep apnoea may be allowed after review) at the time of screening.Patients with gastrostomy at the time of screening.Patients whose clinical efficacy evaluation will not be possible.Patients who fall into or above Class II following the New York Heart Association's functional classification.Patients who received other investigational products or edaravone within 3 months or 5 half-lives at the time of screening.Patients who have experienced epileptic seizures.Patients with severe renal disorders.Patients with severe hepatic disorders.Patients who have haemorrhage tendency at the time of screening.Patients who are found to have active viral infections at the time of screening.Patients with hypersensitivity to antibiotics.Patients who have received any cell therapy product for the same disease.Patients with any malignant tumour in the past 5 years before screening (except malignant tumours with low risk of metastasis or death).Patients who are receiving any medicinal products that may affect bone marrow functions.Patients with any neurological disease other than ALS.Patients with severe mental disorders.Patients under diaphragmatic pacing.Patients for whom the administration of investigational products is prohibited, patients with conditions that may affect the interpretation of results or patients with conditions that may result in a high risk of complications.

### Who will take informed consent? {26a}

Informed consent will be obtained by the principal investigator or delegated sub-investigators at each site. At the beginning of the lead-in period, potential participants will be informed about this clinical trial (purpose, method, procedures, benefit, and potential hazards) and will be provided with a participant information leaflet.

In this clinical trial, several types of informed consent forms (ICFs) for the prescreening, main study, observation study, and data collection of pregnant partners and newborn babies will be prepared.

### Additional consent provisions for collection and use of participant data and biological specimens {26b}

Participants will be asked to consent to their data and biological specimens (peripheral blood, cerebrospinal fluid, bone marrow, etc.) for drug-related biomarkers study.

## Interventions

### The explanation for the choice of comparators {6b}

The control group will receive normal saline (sterilized isotonic sodium chloride solution). Intrathecal administration of normal saline is the most common comparator used in clinical trials for stem cell therapy in neurological disease (NCT03355365, NCT01254539, NCT04749667, NCT04528550, NCT03521323). It has been reported that there are no serious adverse effects, no cells, and it has similar compositions to human body fluid [16].

### Intervention description {11a}

The 115 subjects will be randomized (1:2:2) into three groups: (1) study Group 1 (*n*=23, two injections of Lenzumestrocel at 0 and 26 days and followed by three injections of placebo at 4, 7, and 10 months), (2) study Group 2 (*n*=46, five injections of Lenzumestrocel at 0 and 26 days, 4, 7, and 10 months), and (3) control group (*n*=46, five injections of placebo at 0 and 26 days, 4, 7, and 10 months).

After the initial two injections of Lenzumestrocel or placebo with 26-day intervals, additional three administrations with 3-month intervals will be provided. To determine the potential benefit of three additional Lenzumestrocel treatments and an optimal interval, we will analyse serial ALSFRS-R scores and CSF biomarkers in postmarketing surveillance data. When comparing different treatment intervals (3 to 4, 6 to 8, 12 months), the clinical benefits on ALSFRS-R will be maximized after additional regular treatment with 3- to 4-month intervals, which is consistent with the CSF inflammatory cytokine level findings. Using these data, this phase III clinical trial to confirm the long-term efficacy and safety of Lenzumestrocel will be developed and finally approved by the U. S FDA. To avoid the ethical issue the control group faces, who cannot receive any active treatment during the clinical trial despite the two bone marrow aspirations, all participants will receive two additional intrathecal treatments with a 1-month interval. The purpose of this 6th and 7th intrathecal treatment (at 13 and 14 months after the first administration) is the ethical consideration of the control group. Clinical data will not be opened, and clinical trials will be continued in a blinded state for 2 months until the completion of two Lenzumestrocel treatments for the control group.

Lenzumestrocel is an autologous bone marrow-derived mesenchymal stem cell (BM-MSC) that was isolated, expanded, and analysed under good manufacturing practice (GMP) conditions at Corestem Inc. (Seoul, Korea), based on the International Society of Cellular Therapy guidelines [17]. Details of the manufacturing procedures of Lenzumestrocel are described in our previous phase II paper [14].

Lenzumestrocel will be supplied as a 4 mL MSC cell suspension (1×10^7^ cells per mL of CSF) and prefilled in a syringe. For the allowance of sufficient time for ex vivo MSC expansion, bone marrow extraction will be performed 36 days before the first Lenzumestrocel injection. One day before Lenzumestrocel injection, participants’ own CSF will be collected for use as a suspension. Lenzumestrocel will be delivered to the hospital and will be administered to the participant within 48 h from the completion of the suspension.

Using a standard lumbar puncture at the level of L2–L4, Lenzumestrocel will be slowly injected (total number of MSCs adjusted by body weight, 1×10^6^ cells per kg) intrathecally over approximately 2 minutes. Subsequently, participants will remain in the Trendelenburg position with the application of a mechanical vibrator on their hip bone for 2 h.

All participants will receive continuous riluzole treatment (100 mg/day) except those with side effects. All subjects will be observed for 14 months after the first administration of Lenzumestrocel or placebo.

### Criteria for discontinuing or modifying allocated interventions {11b}

Participants who have withdrawn from the study cannot participate in this study again, but there is no disadvantage due to the withdrawal of the clinical trial for their medical care. Allocated interventions cannot be modified.

Participants may discontinue from the study at any time and for any of the following reasons:Withdrawal of the informed consentDeath of the participantThe decision of the principal investigator or sub-investigator because of safety issues

If the participant does not wish to administer the study drug but to continue participating in the study, it is regarded as the end of treatment, and follow-up is continued.

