### Outcomes {12}

The two primary endpoints are a joint-rank test of function (ALS Functional Rating Scale-Revised) and overall survival (Table 1). The joint-rank test is a robust endpoint for ALS studies because of the ability to interpret death and functional change [18].

**Table 1 Tab1:** Description of primary, secondary, exploratory endpoints and analysis method

Endpoints	Description	Analysis method
Primary	(1) Difference in joint rank scores between study Group 2 and control group at 12 months (2) Difference in joint rank scores between study Group 1 and control group at 6 months	(1, 2) Analysis of covariance (ANCOVA) with adjustment of baseline ALSFRS-R score, baseline ALSFRS-R progression rate, and stratification factors (1, 2) Generalized Gehan-Wilcoxon rank test for supportive analysis
Secondary	(1) Difference in joint rank scores between study Group 2 and control group at 6 months (2) Change from baseline in ALSFRS-R score at 12 months (study Group 2 and control group) (3) Change from baseline in ALSFRS-R score at 6 months (study Group 1 and control group)	(1, 2, 3) ANCOVA with adjustment of baseline ALSFRS-R score, baseline ALSFRS-R progression rate, and stratification factors
	(4) Time-to-event at 12 months (study Group 2 and control group) (5) Time-to-event at 6 months (study Group 1 and control group)	(4, 5) Stratified cox proportional hazards model with adjustment of baseline ALSFRS-R progression rate and stratification factors
Exploratory	(1) Comparison of the change from baseline in SVC score at 6 months (study Group 1 and control group) and 12 months (study Group 2 and control group)	(1, 3, 8, 10) ANCOVA with adjustment of the baseline value, baseline ALSFRS-R progression rate, and stratification factors

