### Plans to promote participant retention and complete follow-up {18b}

There are several alerting systems to keep the planned assessment or procedure schedule. The investigational product order system developed for the study will send a text to the research staff 1 week and 1 day before the planned date to contact the participants to remind them of their schedule. In addition, participants will repeatedly receive the reminder texts through the alerting system of each site at a set time before the planned schedule. Remote evaluation (ALSFRS-R, time-to-event/death, ALSAQ-40, and EQ-5D-5 L) can be conducted for subjects who do not withdraw their consent even though the clinical study is discontinued.

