### Methods in analysis to handle protocol non-adherence and any statistical methods to handle missing data {20c}

Data will be analysed using the intention-to-treat (ITT) set. This set will be applied to all randomized subjects. Subjects will be randomized and analysed for efficacy evaluation.

For the primary and secondary efficacy endpoints, multiple imputation (MI) methods will be used to handle the missing values, if applicable. The multiple imputation method replaces each missing value with a set of plausible values that represent uncertainty and imputation with the right value. The method for imputing variables is available in SAS PROC MI for both monotone and arbitrary missing data patterns and will be implemented with the PREDICT MEAN MATCHING option. In addition, sensitivity analyses will be conducted for the primary efficacy endpoint to examine the impact of missing data using the SAS PROC MI for both monotone and arbitrary missing data patterns using the REGRESSION option.

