### Adverse event reporting and harms {22}

Subjects are instructed to report any adverse events voluntarily, and investigators are responsible for identifying adverse events at regular or additional visits through interviews or medical examinations. Information on adverse events, such as occurrence date, disappearance date, severity, and consequence of the adverse event, actions were taken regarding investigational products, causal relationship with investigational products/concomitant medication, suspected cause other than investigational products and concomitant medication, treatment of the adverse event, and others will be collected and recorded. To identify acute adverse events after administration of investigational products, subjects will be monitored for blood pressure, pulse, body temperature, and respiration at approximately 6-hour intervals for at least 24 h after administration of investigational products. A serious adverse event must be reported to the sponsor within 24 h from the time of the event and acknowledged by the investigator. In addition, especially significant adverse events as defined below will be collected and reported to the sponsor immediately (within 24 h).

Suspected transmission from an infection source by the investigational product as defined below is also considered an especially significant adverse event.

Organisms, viruses, or infectious particles are considered infection sources regardless of pathogenicity. Transmission from an infection source is suspected if a subject exposed to drugs has clinical symptoms or obtains laboratory examination results that imply infection. The term especially significant adverse event is only used when investigational product contamination is suspected. Detailed reporting of serious adverse events is shown in Fig. 2.

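### An investigator's safety decision is classed as leaving the study, against 14-month observation and ITT for all; the remote follow-up that could keep the data is optional and omits adverse events

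*Protocol article*

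**What the plan says.** All references are to the protocol article.

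- **Criteria for discontinuing or modifying allocated interventions {11b}.** The list opens with "Participants may discontinue from the study at any time and for any of the following reasons". It gives three reasons: withdrawal of consent, death, and the "decision of the principal investigator or sub-investigator because of safety issues". A separate sentence deals with a participant who no longer wants the study drug but wants to remain: "it is regarded as the end of treatment, and follow-up is continued".
- **Intervention description {11a}**, repeated under Trial design {8}: "All subjects will be observed for 14 months after the first administration of Lenzumestrocel or placebo".
- **Missing-data section {20c}.** The efficacy analysis uses the intention-to-treat set: "This set will be applied to all randomized subjects". Missing primary and secondary values are multiply imputed by predictive mean matching, with the regression option as a sensitivity analysis.
- **Participant retention {18b}.** "Remote evaluation (ALSFRS-R, time-to-event/death, ALSAQ-40, and EQ-5D-5 L) can be conducted for subjects who do not withdraw their consent", and this applies even where the study has been discontinued.
- **Outcomes {12}.** "The two primary endpoints are a joint-rank test of function (ALS Functional Rating Scale-Revised) and overall survival".
- **Adverse event reporting and harms {22}.** Subjects are told to report events voluntarily, and "investigators are responsible for identifying adverse events at regular or additional visits through interviews or medical examinations". Serious events go to the sponsor within 24 hours.

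**The concern.** The article separates leaving treatment from leaving the study, then puts the safety stop on the study side. Read literally, a patient who still consents but is stopped for safety has a weaker claim to follow-up than one who simply prefers no more injections.

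Two things are at stake. First, safety stops may be related both to treatment and to prognosis. If their 6- or 12-month outcomes are missing, the imputation rests on patients who stayed, and neither imputation method described departs from missing at random. If the lost patients would have done worse than their imputed values, the comparison tilts toward the arm with more safety stops. Second, these are the patients whose later adverse events matter most for an intrathecal cell product, and the Abstract promises safety assessment throughout the study period.

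**Working it through.** **1. The routes side by side.**

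| Route | Class in {11b} | Follow-up stated in {11b} | Remote ALSFRS-R and event/death {18b} | Adverse events in remote list {18b} |
|---|---|---|---|---|
| Consent withdrawn | leaves study | none | not covered | no |
| Death | leaves study | not applicable | outcome known | not applicable |
| Investigator's safety decision | leaves study | none | permitted, not required | no |
| Participant declines dosing | ends treatment | continues | permitted; regular follow-up stands | no, but regular follow-up stands |

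The third row cannot be squared with 14 months of observation for all subjects in {8} and {11a}. It also fits poorly with an all-randomized analysis in {20c} that should rest on observed outcomes where consent allows. {11b} does not refer to {18b}.

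**2. Can the primary outcome be kept?** Yes. The joint rank score needs ALSFRS-R and survival, and both are on the remote list. The gap is that collection is not required and has no stated times.

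**3. Is this a sample-size problem?** The inputs come from Sample size {14}: two-sided alpha 0.05, power 80%, c = 0.5, p'' = 0.769 at 6 months and 0.705 at 12 months.

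N = (1.960 + 0.842)² / [12 × 0.5 × 0.5 × (p'' − 0.5)²]

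- 6 months: 7.849 / (3 × 0.0724) = 36.16, so 19 per arm. 19 / 0.85 = 22.4, so 23.
- 12 months: 7.849 / (3 × 0.0420) = 62.26, so 32 per arm. 32 / 0.85 = 37.6, so 38.

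These reproduce the plan's figures. After the 1:2:2 adjustment the 12-month comparison has 46 per arm. It can lose 46 − 32 = 14 per arm (14/46 = 30%) before it falls below its target. Group 1 can lose 23 − 19 = 4 (4/23 = 17%). Inverting the same formula, 12-month power is Φ(√[12 N c(1 − c)] × 0.205 − 1.96). Assumed losses of 15%, 30% and 35% in both arms give about 0.88, 0.81 and 0.78. The issue is therefore who is lost, not how many.

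**4. How large could the bias be?** The article gives no safety-stop rate, so any figure is an assumption. The illustration uses 46 vs 46, no true effect, all safety stops in Group 2, and every one of them missing at 12 months. The table gives the chance of a result falsely favouring Lenzumestrocel (nominal 2.5%; simulated with no loss 2.4% to 2.9%).

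| Lost in Group 2 | Imputed by random draws from retained Group 2 patients | Imputed by matching on an earlier score |
|---|---|---|
| 4 of 46, from the worst quarter | 9.4% to 9.8% | 4.7% to 4.9% |
| 4 of 46, from the worst half | 6.2% to 6.3% | 3.0% to 3.8% |
| 2 of 46, worst quarter or half | 3.7% to 5.4% | 2.9% to 3.6% |

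The right-hand column is closer to the predictive mean matching that {20c} states. It assumes a correlation of 0.8 to 0.9 between the earlier and the 12-month score; the article does not list the imputation predictors. The left-hand column ignores the stated method and is a worst case only.

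**The case against.** The strongest reply is that this is loose wording in a condensed article. The list in {11b} says participants *may* discontinue, under a heading about interventions. {18b} already covers a safety-stopped patient who keeps consent, and *can* may mean only that a remote assessment may replace a visit. No section says that adverse-event collection stops. {22} keeps voluntary reporting, additional visits and 24-hour serious-event reporting, with no exception for discontinued subjects. The participant timeline is in an additional file and the full protocol is not shown; either may specify follow-up after discontinuation. Earlier trials are described as showing the injections to be safe and well tolerated, and controls undergo the same procedures, so safety stops may be few and balanced.

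Much of this stands. A reader might infer that safety-stopped patients lose their primary outcome and all adverse-event follow-up. The documents do not support that: {18b} allows both components of the endpoint to be collected, and the end of adverse-event collection would be an inference from silence. A reader might also take a false-positive rate near 10% as the expected consequence. That needs one-sided losses from the worst quarter and an imputation that ignores patient history, contrary to {20c}.

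What does not fall away is the conflict in the text itself. {11b} distinguishes study from treatment within a few lines and puts the safety decision on the study side, while {8} and {11a} keep everyone under observation.

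**Conclusion.** The concern holds as an inconsistency between sections with an incomplete fallback. {11b} conflicts with {8} and {11a} on who stays under observation and sits badly with the all-randomized analysis in {20c}. {18b} permits but does not require the assessments that would preserve the primary outcome. No section shown secures adverse-event collection after a safety-based discontinuation.

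The size of the bias cannot be stated. Its direction depends on which arm has more safety stops and on whether those patients fare worse than their imputed values; if stops were rare or balanced, it would be small. The figures above illustrate assumed cases and do not estimate this trial's error rate. The point is still worth acting on, because outcomes not collected cannot be recovered, and the Discussion itself expects that dropout may exceed the planned rate.

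**What to change.** 1. Reconcile {8}, {11a}, {11b}, {18b} and {22} on whether an investigator's safety decision ends treatment or study participation, and state which observation then continues. The clinical rule itself is for the sponsor and investigators; this review proposes none.
2. In {18b}, change *can be conducted* to *will be conducted* at the scheduled assessment times, including months 6 and 12 and through month 14, for every subject who has not withdrawn consent, whatever the reason for stopping. Refer to this from {11b}.
3. Add adverse events and serious adverse events to the remote list in {18b}, and make {22} consistent with it.

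The cost is amended wording and some additional remote contacts with patients who have stopped. The remote route already exists, and sample size and analysis model do not change. Recruitment was under way at publication, so the change protects only assessments still to come.
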